## Introduction

 Malnutrition underlies 45% of child deaths and has far-reaching educational, economic and health consequences.^1^ Severe acute malnutrition (SAM), characterised by severe muscle wasting and/or presence of nutritional oedema, affects 13.7 million children globally and is the most life-threatening form of malnutrition.^2^ Community-based management of acute malnutrition using ready-to-use therapeutic food (RUTF) has transformed outcomes for children with uncomplicated SAM, but those presenting with poor appetite or medical complications (categorised as having ‘complicated’ SAM) require hospitalisation and often have poor outcomes despite medical and nutritional management.^3^ Mortality among children with complicated SAM in sub-Saharan Africa remains at 10%–20% in hospital^4^ and 10%–15% in the year post-discharge.^5^

Comorbidities often complicate the management of children hospitalised with SAM. Children with HIV and SAM have threefold higher mortality than children with SAM alone, and this excess risk of death persists despite antiretroviral therapy (ART).^5^ Children with cerebral palsy, hydrocephalus and other neurodisabilities have a high risk of SAM due to difficulties in feeding and additional energy needs. In the recent Health Outcomes, Pathogenesis, and Epidemiology (HOPE)-SAM study, on discharge from hospital, children with cerebral palsy had a sixfold higher risk of mortality than children without cerebral palsy.^5^ Stunting is often coincident with wasting and compounds the risk of mortality and readmission to hospital after initial management of complicated SAM.^6^ A study in Malawi showed decrements in physical and cognitive function were apparent 7 years after hospitalisation with SAM, which may increase long-term non-communicable disease risk.^7^ Taken together, there is substantial evidence that SAM is not a single condition due to lack of food but is rather a complex syndrome, characterised by multimorbidity, and that current long-term outcomes are unacceptably poor.

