#### Screening and enrolment

Children with complicated SAM will be screened and enrolled from hospitals once they have stabilised after their admission. Children of either sex will be eligible if they are age 6–59 months, hospitalised with complicated SAM (per WHO definitions),^3^ have started the transition from therapeutic milk feeds to RUTF, and have a caregiver who is willing and able to give informed consent and to attend all study visits. Children will not be eligible if they have any acute or chronic condition which means that receipt of study interventions, or participation in the trial, would not be advisable.

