#### Baseline procedures

Following enrolment, baseline procedures will be conducted while the child is still hospitalised, prior to randomisation. Demographic, child and caregiver data will be collected, and children will undergo clinical examination, review of medical history and current medications, HIV testing (if not done previously), TB diagnostics (if not done previously) and anthropometry. Blood will be collected to measure baseline liver function and to store plasma and leucocytes. Stool will be collected and stored for subsequent measurement of enteropathy biomarkers.

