#### Interim analysis

One interim analysis will be undertaken once the following three conditions are achieved: (1) at least one active intervention arm reaches 106 participants; (2) the smallest active intervention arm reaches at least 50 participants; and (3) all four intervention arms are active. A logistic regression model accounting for country, age, sex and baseline oedema with indicators for each active treatment will be fitted on the composite primary outcome. If the test statistic falls below the lower (futility) bound of zero in an arm, indicating that there is no benefit of that arm over control, then that arm may be discontinued. Similarly, if the test statistic of an arm exceeds the upper (efficacy) bound (2.693), then that arm may be discontinued as it clearly suggests substantially lower mortality, hospitalisation or failed nutritional recovery than the control group. Active arms that have test statistics between the lower and upper bound will be continued, as they suggest potential benefit. The boundary estimates (0 and 2.693) have been calculated to control for the family-wise error. All decisions about dropping arms will be made in conjunction with the Data Monitoring and Ethics Committee, which comprises four independent members, and Trial Steering Committee, which comprises five independent members.

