#### Final analysis

The primary analysis will include all participants as randomised (‘intention-to-treat’), irrespective of whether they received their allocated treatment. Both treatment effects and 95% CIs will be reported for all primary, secondary and subgroup analyses. The per-protocol analysis is a secondary analysis and will include all children without major protocol violation who had the primary outcome measured. Final analyses will be undertaken once 24-week data are available for at least 211 children in each active arm selected to continue to the second stage, and at least 422 control children. A logistic regression model with country, age, sex and oedema status as covariates, and a treatment indicator for each intervention, will be fitted. From the model, test statistics will be computed to compare each active arm to the control arm. If the test statistic exceeds the critical value of 1.904, then the corresponding arm will be identified as a promising intervention. Secondary outcomes will be evaluated using the same principles and critical values as the primary analysis. A linear regression model will be used for continuous outcomes (transformed if required); a logistic regression model will be used for binary outcomes; and a proportional hazards model will be used for time-to-event outcomes. If there are substantial missing data, the mechanism will be explored and appropriate methods (eg, multiple imputation) implemented to remove potential inference bias. Statistical code for the main analyses will be made available with the primary publication. The final trial dataset will be made open access at ClinEpiDB after the analyses in the protocol have been reported.

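### The interim and final logistic models leave out baseline HIV status, which the trial already establishes before randomisation; prespecifying it would be a modest, nearly free gain, not the repair of an error

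*Protocol article*

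**What the plan says.** Under Final analysis the article states: "A logistic regression model with country, age, sex and oedema status as covariates, and a treatment indicator for each intervention, will be fitted". Under Interim analysis it states: "A logistic regression model accounting for country, age, sex and baseline oedema with indicators for each active treatment will be fitted". Both lists contain the same four baseline covariates, and neither contains HIV status. Randomisation is stratified by hospital site only (Randomisation).

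The Introduction says: "Children with HIV and SAM have threefold higher mortality than children with SAM alone". It adds that the excess risk persists despite antiretroviral therapy. On neurodisability it says that after discharge "children with cerebral palsy had a sixfold higher risk of mortality than children without cerebral palsy".

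On timing, "baseline procedures will be conducted while the child is still hospitalised, prior to randomisation", and the procedures listed include "review of medical history and current medications, HIV testing (if not done previously), TB diagnostics (if not done previously) and anthropometry". HIV status is therefore a genuine pre-randomisation variable that the trial already obtains. Cerebral palsy is not named among the baseline items.

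**The concern.** The article singles out HIV as a strong determinant of mortality in this population and sets up its baseline visit so that HIV status is known. It then leaves HIV out of both the stratification and the model. Adjusting a logistic test for a prognostic baseline variable usually raises the expected test statistic under the alternative. It also removes the part of chance imbalance between arms that is due to that variable. At stake is some power at the final critical value of 1.904. To a lesser degree the interim is affected too, because an arm with as few as 50 children is compared there with a futility bound of zero.

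**Working it through.** **1. The plan's own power figure.** Inputs from Sample size, Interim analysis and Final analysis: control risk 35%; a 30% relative reduction, so 0.35 × 0.70 = 24.5%; 422 control and 211 per active arm; bounds 0 and 2.693 at interim and 1.904 at the end; 5% loss.

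- Unpooled standard error at 422 vs 211: √(0.35×0.65/422 + 0.245×0.755/211) = 0.0376. Expected z = 0.105/0.0376 = 2.79.
- Two-stage pairwise power, with the interim at half the information (assumed): about 81%. After 5% loss (401 vs 200.5) it is about 79%.
- Simulated family-wise error of the design: 0.1005, against the stated 0.10.

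The stated 80% therefore reproduces to within about a point either way, with no contribution from covariates.

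**2. Gain from adding HIV alone.** The article gives no HIV prevalence and no HIV effect on the composite, so both are assumed over a range. For each pair, the intercept and treatment effect were solved so that the marginal risks stay at 35% and 24.5%. The large-sample logistic Wald statistic was then computed with and without HIV at 401 vs 200.5, with power = Φ(z − 1.904).

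Without HIV, the log odds ratio is −0.506 with standard error 0.195, so |z| = 2.600 and power is 75.7%. This is a single-stage log-odds calculation without the other covariates. It is lower than the figures in step 1 because it uses a different statistic, so only the difference between models should be read from it.

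| HIV prevalence | OR 1.3 | OR 1.5 | OR 2 | OR 3 |
|---|---|---|---|---|
| 10% | +0.1 | +0.1 | +0.4 | +1.1 |
| 20% | +0.1 | +0.2 | +0.7 | +1.9 |
| 30% | +0.1 | +0.3 | +0.9 | +2.3 |

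(Percentage points of power; OR is HIV's odds ratio on the composite.)

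In the most favourable cell the adjusted |z| is 2.678 and power is 78.0%. The equivalent saving in sample size is (2.678/2.600)² − 1 = 6%, or about 0.06 × 1266 = 76 children. In the least favourable cell it is about 0.1%. The gain comes through the ratio: in that best cell the adjusted log odds ratio moves from −0.506 to −0.537 while its standard error also rises, from 0.195 to 0.201.

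**3. Which odds ratio is plausible?** The article puts mortality at 10% over 12 months (Risks and benefits), while the composite control rate is 35% by 24 weeks. Most composite events must then be non-fatal. If the threefold ratio acts on death alone, with 24-week mortality assumed at 5–10%, HIV's implied composite odds ratio is about 1.2–1.6, which lies towards the left of the table.

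**4. Chance imbalance.** For a factor with assumed prevalence 20%, the standard deviation of the difference between arms is √(0.2×0.8×(1/422 + 1/211)) = 3.4 points at the end. At the interim, with an assumed 212 controls, it is √(0.16×(1/50 + 1/212)) = 6.3 points for an arm of 50. At OR 3 and 20% prevalence, control-arm risks are 56.0% and 29.8%, a gap of about 26 points. A one-SD imbalance at the end then moves the risk difference by 0.034 × 0.26 = 0.9 points, against a standard error of 3.8 points.

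**5. Type I error.** In 4,000 simulated two-stage trials under the null, with HIV at 20% and odds ratio 3 and cerebral palsy at 6% and odds ratio 6, family-wise error was 0.107 without the two factors in the model and 0.106 with them.

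**The case against.** The strongest reply is that nothing here is wrong. A short prespecified covariate list is legitimate. Leaving a baseline variable out of a randomised comparison neither biases it nor raises type I error, chance imbalance is already reflected in the standard error, and the 80% power never relied on covariates. All of this stands, and it is why the point is an improvement and not a defect. It does not remove the case for using a variable that is already collected and has no type I error cost.

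Two stronger readings are tempting, and the article supports neither.

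- **Material power is being given away.** A reader might carry the threefold and sixfold ratios over to the primary outcome. Doing so, as composite odds ratios of 3 and 6 with HIV at 20% and cerebral palsy at 6%, gives a simulated rise from 75.6% to 79.5%. But the ratios are for mortality. A sixfold risk ratio on the composite is not credible: if affected children cannot exceed 100% risk, the others cannot exceed 1/6, and an overall 35% then needs a prevalence of at least (0.35×6 − 1)/5 = 22%. With composite odds ratios of 1.4 and 1.8 instead, the same simulation gives 76.4% to 76.7%.
- **Cerebral palsy belongs in the model on the same footing as HIV.** It is not a named baseline item and would have to come from history or examination. Entry criteria may also remove some of these children: "Children will not be eligible if they have any acute or chronic condition which means that receipt of study interventions", or participation itself, would be inadvisable.

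In the other direction, treating HIV as acting on death alone is probably a floor. The Reformulated RUTF section describes metabolic and inflammatory disturbance as especially marked in children with HIV, which could also bear on nutritional recovery. The article does not quantify this.

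On the interim, crossing zero permits an arm to be stopped but does not oblige it. The decision is taken with the monitoring and steering committees, and no separate interim power loss has been calculated here.

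**Conclusion.** The point holds as a modest, optional improvement. Both primary models omit HIV status although the article itself identifies it as prognostic for death and has it known before randomisation. The gain from adding it is about 0 to 2.3 percentage points of power (about 0–6% of sample size), assuming prevalence 10–30% and a composite odds ratio of 1.3–3. It is no more than about 0.3 points if the composite odds ratio is only 1.3–1.5. These ranges are assumptions, since the article supplies neither quantity. The validity of the comparison, its error rate and the stated power are unaffected. The case for neurodisability is conditional on its being recorded at baseline.

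**What to change.** Before any analysis, add baseline HIV status (positive / negative / exposed or unknown) as a prespecified covariate in both the interim and the final logistic model, with a rule for merging a category that turns out to be very small. Add cerebral palsy or other neurodisability (yes/no) only if the baseline case report form records it in a usable way. Keep the bounds 0, 2.693 and 1.904 as they are, and describe any expected gain as modest and dependent on assumptions.

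For HIV no new data collection is needed. The article says the analysis plan will be posted before any analyses, so the change may need only wording there. If the full protocol fixes the same four covariates, it becomes an amendment, which the article says requires approval by the regulators in each country and the sponsor.

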### Sample size

For the primary analysis, a total sample size of 1266 participants across all three countries, with a final ratio of 2:1:1:1:1 in favour of standard-of-care, provides 80% power to detect a 30% reduction in the composite primary outcome of death or hospitalisation or failed nutritional recovery within 24 weeks, assuming a control arm event rate of 35% with overall one-sided alpha of 0.10 (ie, family-wise error),^32^ allowing for 5% loss to follow-up if all arms start at the same time. The control arm event rate was based on published data on mortality, readmission and nutritional recovery from the HOPE-SAM study^5 33^ in Zimbabwe and Zambia, and the Childhood Acute Illness and Nutrition network,^13 34^ which included sites in east Africa. Children who are enrolled but not randomised for any reason will be replaced.

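### The single final bound of 1.904 is valid but leaves part of the 10% family-wise error unused once any arm works; a pre-specified step-down test would recover some power at no extra sample

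*Protocol article*

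**What the plan says.** The Sample size section sets an "overall one-sided alpha of 0.10 (ie, family-wise error"). It plans for 1266 children, with control allocated twice as many as each of the four active arms, and claims that this "provides 80% power to detect a 30% reduction in the composite primary outcome". The control risk is fixed by "assuming a control arm event rate of 35" per cent, and the total is described as "allowing for 5% loss to follow-up if all arms start at the same time".

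The Interim analysis section applies a futility bound of 0 and an efficacy bound of 2.693 to every arm. It says that these were calculated to control the family-wise error.

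The Final analysis section requires 24-week data on "at least 211 children in each active arm selected to continue to the second stage, and at least 422 control children". It then applies one value to every arm: "If the test statistic exceeds the critical value of 1.904, then the corresponding arm will be identified as a promising intervention". It carries the same critical values over to the secondary outcomes and reports 95% confidence intervals throughout.

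No section lowers the bound for the remaining arms after another arm has succeeded. The Randomisation section changes only the allocation ratio when an arm is dropped.

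**The concern.** A bound of 1.904 is the price of four null hypotheses that are all true together. Once one arm has been shown to work, at most three can still be true, and the same 10% family-wise error allows a lower bound for the next arm. The plan charges every arm the full four-arm price whatever the others show.

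A step-down (closed) test rejects everything that the single-step rule rejects, and sometimes more, under the same strong error control. The difference matters only if several packages work. The Objectives section hypothesises a benefit for each package, and the combined arm contains the other three, so that case is relevant here. What is at stake is a missed effective arm, in particular a single component whose result bears on whether the whole package is needed.

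**Working it through.** **Inputs.** Four active arms; final numbers 211 per active arm and 422 controls (6 × 211 = 1266); one-sided family-wise error 0.10; control risk 0.35; 30% relative reduction, so 0.35 × 0.70 = 0.245 and a difference of 0.105; 5% loss, giving about 401 controls and 200 per active arm; interim bounds 0 and 2.693.

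**Assumptions.** The interim falls at half the information (106 of 211 is about one half), all arms start together, and the futility rule is followed.

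**1. Reproduce the plan's bounds.** Two arm-versus-control statistics share the control group, with correlation 211/(211 + 422) = 1/3. Let Z1 be the interim statistic and Z the final one. An arm is not rejected if Z1 < 0, or if 0 ≤ Z1 < c√2 and Z < c. Conditional on the control data the arms are independent, so the family-wise error under the global null is 1 − E[P(arm not rejected | control)^K]. Setting this to 0.10 with K = 4 gives c = 1.9043 and c√2 = 2.6930, which are the stated 1.904 and 2.693. At exactly 1.904 the error is 0.1001.

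**2. Reproduce the power.** With unpooled variance and 401/200 evaluable, the standard error is √(0.35 × 0.65/401 + 0.245 × 0.755/200) = √(0.000567 + 0.000925) = 0.0386. The drift is 0.105/0.0386 = 2.72. Ignoring the interim, power is Φ(2.72 − 1.904) = 79%; with the interim rules it is 79.1%. With 422/211 evaluable it is 81.1%. The stated 80% is reproduced. A log-odds drift of 2.60 gives about 76%.

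**3. Bounds for fewer arms.** Solving the same design again gives final bounds of 1.793 (K = 3), 1.628 (K = 2) and 1.321 (K = 1). The rule recommended here uses 1.904, 1.793, 1.645 and 1.645. The floor of 1.645 is stricter than the exact values for two arms and one arm, and keeps every claim at one-sided 5% or better. Only a rejection moves to the next bound; arms dropped for futility remain in the count as not rejected.

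**4. Compare the two rules.** Normal-theory simulation with 1,000,000 trials per scenario, drift 2.72 in each effective arm and 0 in the others, interim bounds unchanged. Each cell shows single-step → step-down with floor.

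| Effective arms | Power per effective arm | All effective arms found | At least one found | Any false claim |
|---|---|---|---|---|
| 0 | – | – | – | 10.0% → 10.0% |
| 1 | 79.1% → 79.2% | 79.1% → 79.2% | 79.1% → 79.2% | 7.9% → 9.6% |
| 2 | 79.1% → 81.2% | 65.6% → 69.8% | 92.6% → 92.6% | 5.5% → 8.9% |
| 3 | 79.1% → 83.5% | 56.1% → 66.6% | 96.6% → 96.6% | 3.0% → 4.9% |
| 4 | 79.1% → 84.4% | 49.0% → 60.5% | 98.1% → 98.1% | – |

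Repeat runs differ by about half a point at most (for example 84.4% to 85% per arm with four effective arms, and 9.6% to 9.7% false claims with one). With very strong effects in one, two or three arms, the chance of a false claim under the recommended rule was 9.7%, 9.2% and 5.0%, still within 10%.

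**5. Without the floor.** Using 1.628 and 1.321 for the last two bounds gives, with four effective arms, about 87% per arm and 71 to 72% for all four. Roughly half of that all-arms gain (about 22 to 23 points over 49%) is given up by the floor, which gains about 12.

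**The case against.** The strongest reply is that nothing here is wrong. Single-step testing is a legitimate choice that decides each arm on its own data; 1.904 is computed correctly, and the rule delivers about the 80% per arm that the plan promises. The plan never promises to find all effective arms, so 49% or 56% is no shortfall against a stated target. All of this stands, and it limits the point to an efficiency suggestion.

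The gain also has a price. False claims rise from the lower single-step level. With one effective arm that rise (7.9% to about 9.7%) buys no useful power; with two, 2 points per arm are bought with a rise from 5.5% to 8.9%. A lower-ranked arm could be called promising at a statistic between 1.645 and 1.904 only because another package succeeded, while its reported 95% interval includes no effect. That mismatch exists already for statistics between 1.904 and 1.96, but it would widen. A sponsor that already works at a lenient one-sided 10% may reasonably decline.

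A reader might infer that the trial expects all four arms to work at the full 30%, which is where step-down gains most. The documents do not go that far: the Objectives section states a hypothesis for each arm, the Safety section states equipoise for all interventions, and the design is built around dropping unpromising arms.

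**Conclusion.** The point holds as a cheap improvement. The stated bound is valid but conservative once any arm is effective. The recommended step-down rule keeps the family-wise error at or below 10% in every scenario examined and raises power per effective arm by about 0, 2, 4 to 5 and 5 to 6 points with one, two, three and four effective arms. The chance of finding every effective arm rises by about 4, 11 and 12 points with two, three and four.

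Two stronger readings are not supported. First, 1.904 is not an error, and the trial does not fall short of its stated power. Second, the gains to about 87% per arm and 72% for all four belong to the version without the 1.645 floor, in which a last arm could be claimed at 1.321 (one-sided p about 0.09); that version is not the one proposed.

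The figures rest on a simultaneous start, half information at the interim, the futility rule being followed, and a drift of 2.72. The article introduces arms in stages and allows as few as 50 children in the smallest arm at the interim, so the constants will change; this applies equally to 1.904. The article also says only that an arm below zero may be discontinued. If futility is ignored, the error at 1.904 is 10.1% and the exact bounds become 1.910, 1.800, 1.639 and 1.343.

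**What to change.** In the Final analysis section and the analysis plan, before any analysis:

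- Order the arms by test statistic, compare them in turn with 1.904, 1.793, 1.645 and 1.645, and stop at the first arm that fails.
- Count every arm that crosses 2.693 at the interim as a rejection. Keep arms dropped for futility in the count as not rejected. Leave both interim bounds unchanged.
- Recompute all constants, including 1.904, for the allocation and information actually available in each arm.
- State whether the step-down rule also governs the secondary outcomes, which now inherit the primary critical values.
- State that the reported 95% intervals are descriptive and need not agree with the decision for lower-ranked arms.

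The cost is a few sentences and one recalculation. The total stays at 1266, with no extra visits and no change to the interim. The statistical cost is the rise in false claims within the 10% budget shown above. If the sponsor prefers the single-step rule, one sentence giving that choice and its reason is enough.

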Death or first hospitalisation or failed nutritional recovery within 24 weeks post-randomisation	All-cause mortality or overnight admission to a health facility for any reason*, or failed nutritional recovery† within 24 weeks of randomisation

Secondary outcomes	
Change in weight-for-height Z-score between baseline and 24 weeks post-randomisation	Change in weight-for-height Z-score between baseline and 24 weeks post-randomisation according to age-appropriate and sex-appropriate WHO reference standards
Change in mid-upper arm circumference between baseline and 24 weeks post-randomisation	Change in size of mid-upper arm in centimetres between baseline and 24 weeks
Change in weight-for-age Z-score between baseline and 24 weeks post-randomisation	Change in weight-for-age Z-score between baseline and 24 weeks post-randomisation according to age-appropriate and sex-appropriate WHO reference standards
Change in height-for-age Z-score between baseline and 24 weeks post-randomisation	Change in height-for-age Z-score between baseline and 24 weeks post-randomisation according to age-appropriate and sex-appropriate WHO reference standards
Suspected or confirmed tuberculosis, pneumonia, diarrhoea or malaria through 24 weeks post-randomisation	Physician-diagnosed suspected or confirmed infection, as defined by WHO guidelines, between baseline and 24 weeks post-randomisation

Tertiary outcomes	
Change in anthropometry between baseline and 4 weeks post-randomisation	Change in WHZ, WAZ, HAZ and MUAC between baseline and 4 weeks post-randomisation
Change in anthropometry between baseline and 12 weeks post-randomisation	Change in WHZ, WAZ, HAZ and MUAC between baseline and 12 weeks post-randomisation
Change in caregiver mental health between baseline and 24 weeks post-randomisation	Change in Shona Symptom Questionnaire score (and proportion meeting cut-off score >8) between baseline and 24 weeks post-randomisation
Mechanistic laboratory endpoints	Exploratory endpoints based on comparing lipidomic, metabolomic, inflammatory and proteomic signatures between arms

* Includes cases where there was a clinical plan to hospitalise the child, which was refused by the caregiver.

† Defined as either: (i) persistent WHZ <–2 or MUAC <12.5 cm or bilateral pedal oedema at week 12; or (ii) WHZ <–2 or MUAC <12.5 cm or bilateral pedal oedema at any time between baseline and week 24 post-randomisation in a child who had previously recovered.

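### The primary logistic model omits baseline WHZ and MUAC, which gives up some power at interim and final; for the change-score models the article does not say whether the baseline value is included

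*Protocol article*

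**What the plan says.** The article names the primary model twice. Under Interim analysis: "A logistic regression model accounting for country, age, sex and baseline oedema with indicators for each active treatment will be fitted". Under Final analysis: "A logistic regression model with country, age, sex and oedema status as covariates, and a treatment indicator for each intervention, will be fitted". Both lists are explicit, and neither contains WHZ or MUAC.

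Both measures are available. Baseline procedures are completed before randomisation and include "TB diagnostics (if not done previously) and anthropometry". Table 1 needs baseline WHZ and MUAC for its change outcomes, so both are recorded. The second footnote to Table 1 builds failed nutritional recovery on them; its first limb is "persistent WHZ <–2 or MUAC <12.5 cm or bilateral pedal oedema at week 12".

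Four of the five secondary outcomes in Table 1 are changes in anthropometry, for example "Change in weight-for-height Z-score between baseline and 24 weeks post-randomisation"; the others are MUAC, weight-for-age and height-for-age. On their analysis, the Final analysis section says "Secondary outcomes will be evaluated using the same principles and critical values as the primary analysis" and then names the model: "A linear regression model will be used for continuous outcomes (transformed if required". It lists no covariates for that model.

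**The concern.** Failed nutritional recovery can be met on any of three criteria: WHZ, MUAC or oedema. The primary model adjusts for the baseline state of oedema and not for the other two. A child who starts further below a threshold plausibly has further to go by week 12, so baseline WHZ and MUAC can be expected to predict the outcome. Randomisation is stratified by hospital site only, so the design does not balance them.

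What is at stake is efficiency. In a logistic model, leaving out a prognostic covariate pulls the treatment odds ratio towards one and lowers the power of its test. The same test statistic is used at the interim, where a value below zero may end an arm.

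The change-score outcomes raise a related question. If their models carried only the primary covariate set, the outcome's own baseline value would be missing, and the treatment estimate would usually have a larger variance than it needs to have.

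**Working it through.** **1. Reproducing the plan's own figures.** Inputs from Sample size, Interim analysis and Final analysis: N = 1266 at 2:1:1:1:1, so 1266/6 = 211 per active arm and 422 control; control rate 0.35; 30% reduction, so 0.35 × 0.7 = 0.245; bounds 0, 2.693 and 1.904.

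- Pooled rate: (2 × 0.35 + 0.245)/3 = 0.315. Null SE: √[0.315 × 0.685 × (1/422 + 1/211)] = 0.0392.
- SE under the alternative: √[0.35 × 0.65/422 + 0.245 × 0.755/211] = 0.0376.
- Power = Φ[(0.105 − 1.904 × 0.0392)/0.0376] = Φ(0.81) ≈ 79.1%.
- A four-arm, two-stage simulation with the three bounds and half the information at interim gives a family-wise error of 0.0999. Power with unpooled variance is 81.0% for one effective arm (80.2% in the least favourable configuration). With pooled variance it is 77.9%.

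The stated 80% power and 0.10 error rate are therefore reproduced to within about two points.

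**2. Gain from adding baseline anthropometry to the primary model.** The article gives no prognostic strength, so it is assumed. One standard-normal covariate stands for the baseline anthropometry. Each setting used 3,000 simulated trials at 422 v 211 with critical value 1.904, fitted with and without the covariate and with no other covariates.

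| Log-odds ratio per SD (assumed) | AUC | Power without | Power with |
|---|---|---|---|
| 0 | 0.50 | 79.0% | 79.1% |
| 0.3 | 0.58 | 79.8% | 80.2% |
| 0.5 | 0.63 | 79.8% | 81.3% |
| 0.8 | 0.70 | 79.4% | 83.6% |
| 1.1 | 0.76 | 79.3% | 86.3% |

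The Monte Carlo SE of each entry is √(0.8 × 0.2/3000) ≈ 0.7 points. The gain runs from 0.4 to 7.0 points. At 400 v 200, roughly the numbers left after 5% loss, a separate run of 4,000 trials per setting gave 76.2% to 78.6%, 76.5% to 79.9% and 76.8% to 83.5% for log-odds ratios of 0.5, 0.7 and 1.0.

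**3. Change outcomes, if the baseline value is not in the model.** Let r be the correlation between baseline and week 24, and k the baseline SD divided by the week-24 SD. In units of the week-24 variance:

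- change score: 1 + k² − 2rk;
- baseline-adjusted: 1 − r²;
- difference: (k − r)², which is never negative.

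With k = 1 the ratio is (1 − r²)/[2(1 − r)] = (1 + r)/2. For r = 0.3, 0.5, 0.7 and 0.9 that is 0.65, 0.75, 0.85 and 0.95, so the SE is 19%, 13%, 8% and 2.5% smaller. Over the same range of r, the SE gain is 0–11% with k = 0.8 and 20–29% with k = 1.25. In week-24 SDs, the difference detectable with 80% power is (1.904 + 0.842) × √(1/422 + 1/211) × √variance. With k = 1 it falls from 0.23 to 0.20 at r = 0.5, and from 0.18 to 0.165 at r = 0.7.

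**The case against.** The strongest reply is that the planned model is a legitimate pre-specified choice. It adjusts for four covariates, one of them a component of failed recovery, and it neither biases the estimate nor disturbs the error rate. That is correct, and it limits this point to efficiency. The power comparison also starts from a model with no covariates. The four planned ones may already capture part of the gain, and nothing in the article allows that part to be worked out.

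Several stronger readings are tempting but not supported:

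- **That the change-score models omit the baseline value.** A reader may infer this from the reference to the same principles, but that wording does not fix a covariate set for four outcomes with different baselines. The article neither includes nor excludes the baseline value, and such detail is commonly left to the analysis plan, which is announced but not shown.
- **That precision is lost in the primary model.** In logistic regression a prognostic covariate does not shrink the SE of the log-odds ratio. The gain is in power, because the conditional effect is larger.
- **That WHZ and MUAC are the strongest predictors available.** The article gives no such evidence. The risk factors in its Introduction are HIV, cerebral palsy and stunting, and it does not give the shares of the composite's components.
- **That baseline imbalance passes in full into an unadjusted change score.** With equal SDs only a fraction (1 − r) does so, with opposite sign, and it is chance error, not bias.
- **That the later arms are already short of power.** The 80% figure is conditional on all arms starting together, but Final analysis also requires at least 211 children in each continuing arm. A shortfall is not established here.

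**Conclusion.** The point holds as one of efficiency. The primary model at both looks leaves out two pre-randomisation measures whose later values help define the outcome, and so gives up some power. At 422 v 211 the gain from adding them is under one point if they are weakly prognostic and about seven points at a log-odds ratio of 1.1 per SD. These figures rest on an assumed strength and on a comparator without covariates, so the gain over the actual planned model may be smaller. The stated sample size, bounds and error rate stand.

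For the four change outcomes the conclusion is conditional. If the models carry only the primary covariate set, adding each outcome's baseline value cannot increase the variance in large samples. The gain depends on r and k, which the article does not give. It is small when r is high or when the baseline SD is smaller than the week-24 SD; the latter is plausible because entry is restricted to children with complicated SAM.

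**What to change.** Before any analysis, keep the four planned covariates and add baseline WHZ and baseline MUAC as continuous terms to the primary logistic model, in the same form at interim and final. For each change outcome, state that the model includes the baseline value of that measure, and add it if it is not already there.

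No new data are needed. The error-rate check in the working uses only the bounds, the allocation ratio and the information split, none of which this change touches. The reported odds ratio becomes conditional on two more covariates, and the report should say so. The cost is analysis plan wording or a protocol amendment. Enrolment is under way, and the article says under Time frame and study status that amendments need approval from the regulators in each country and from the sponsor, so the cost is modest but not nil. The change should be settled before the interim analysis, because choosing covariates after outcome data have been seen would not be credible.
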